#### Description of baseline characteristics and homogeneity of the two groups

For the description of baseline characteristics, the mean with standard deviation or range with minimum and maximum for continuous data and frequency with percentage for dichotomous data will be reported. For the homogeneity test of the baseline characteristics between the two groups, a two-sample *t*-test for continuous data and a *χ*^2^ test for dichotomous data will be performed. If there are baseline characteristics showing statistical significance between groups, analysis of covariance (ANCOVA) or logistic regression will be used for analysis and adjustment of baseline characteristics.

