### Randomization

After signing an informed consent and undergoing the screening test, the participants in each hospital will be randomly assigned to one of the two groups using block randomization. Random numbers will be generated using the PROC PLAN of SAS 9.2 (SAS Institute Inc., Cary, NC, USA) by an independent statistician and sent to the Acupuncture and Meridian Science Research Center (AMSRC) at Kyung Hee University where the each randomization number will be put in a sequentially numbered opaque envelope and remain sealed by an administrative staff who is otherwise not involved in the study.

Once a participant passes the screening test, the investigator will call the AMSRC staff who is responsible for this randomization process to give her the hospital name, and the initial and screening number of the participant. The AMSRC staff will then immediately fax a document containing a unique random number and participant group allocation. This feedback document will be kept in the trial master file.

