### Sample size calculation

Sample size was determined based on our clinical experience and previous reports where the waitlist group achieved approximately 28% of the PR in patients with irritable bowel syndrome [49]; in our study, we expected that 60% of the participants on the acupuncture arm would achieve adequate relief for over a half of the study period while up to 25% of those on the waitlist arm would achieve such an outcome. Generally, a level of significance of α?=?0.05 and a power of 1–β?=?0.80 were used. The sample size in this trial was estimated according to the following formula where (p_t_?+?p_c_)/2:

$$\begin{array}{l} n=\;{\left(Z_{a/2}\sqrt{2\bar{p}\left(1-\bar{p}\right)}+\;\mathrm{Z\beta}\sqrt{p_{t}\left(1-p_{t}\right)+p_{c}\left(1-p_{c}\right)}\right)}^{2}\\ \;/{\left(p_{t}-\;p_{c}\right)}^{2} \end{array}$$

Assuming p_t_?=?0.6 (p_t_: the effect of the acupuncture group) and p_c_?=?0.25 (p_c_: the effect of the waitlist group), a sample size of *n*?=?30.1 is calculated to achieve 5% of significance level and 80% power. Considering an assumed dropout rate of 20%, a total of 76 participants will be needed with 1:1 allocation to each group (38 participants per group). First, both centers will respectively recruit 30 patients each. After that, the remaining 16 patients will be recruited and randomized competitively to include 76 patients in total.

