### Statistical analysis

A statistical analysis will be performed by an independent statistician who is blinded to group allocation using SPSS 21.0 (IBM SPSS Statistics, New York, USA). Our independent statistician will have an access to the final dataset which will be kept locked so that investigators will have limited access. All data will be presented as means and standard deviations or number (%), and all analyses will be based on an intention-to-treat principle. For intention-to-treat analysis, the last observation carried forward rule will be applied. The statistical significance level will be set at 0.05 (two-sided), with the 95% confidence intervals.

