#### Primary outcome

The primary outcome, PR at 4 weeks, will be compared between groups using the *χ*^2^ test or logistic regression.

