#### Secondary outcomes

Repeated measure two-factor analysis will be used to analyze the difference and mean change among baseline, 4 and 8 weeks, difference and mean change between groups, and interaction between groups and observed time. For dichotomous outcomes, the *χ*^2^ test or logistic regression will be used. For the comparison of adverse events (AEs) between groups, the *χ*^2^ test or Fisher’s exact test will be performed.

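### Baseline significance tests decide whether the analysis is adjusted and for what, so chance selects the model and a prognostic covariate is usually left out

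*Protocol article*

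**What the plan says.** All the relevant text is in the protocol article.

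- **Baseline tests.** The section on baseline characteristics plans a t-test for continuous variables and a χ² test for dichotomous ones: "For the homogeneity test of the baseline characteristics between the two groups". It gives no list of variables.
- **Trigger.** The same section then states: "If there are baseline characteristics showing statistical significance between groups, analysis of covariance (ANCOVA) or logistic regression will be used".
- **Primary analysis.** The Primary outcome paragraph under Statistical analysis reads "The primary outcome, PR at 4 weeks, will be compared between groups using the" χ² test or logistic regression. It names no covariate and gives no rule for choosing between the two. The only rule in the article that could decide is the baseline trigger.
- **Secondary analysis.** "Repeated measure two-factor analysis will be used to analyze the difference and mean change among baseline, 4 and 8 weeks", with group, time and their interaction. Baseline is therefore one level of time, not a covariate.
- **Significance level.** "The statistical significance level will be set at 0.05 (two-sided), with the 95% confidence intervals". No other level is stated, so I take it to apply to the baseline tests as well.
- **Randomisation.** "the participants in each hospital will be randomly assigned to one of the two groups using block randomization". Hospital is therefore a randomisation stratum, yet no stated model contains it.

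**The concern.** If allocation is sound, every baseline difference between the groups is due to chance, and a test of that difference has no bearing on whether the variable predicts outcome. Adjustment pays off when a covariate is prognostic. The rule selects on observed imbalance instead, so an irrelevant variable can enter and a strong predictor will usually stay out.

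Two things are at stake. One is precision, in a trial of 76 participants whose baseline measures are collected anyway. The other is what the primary result means: a χ² comparison gives a marginal contrast of proportions, while an adjusted logistic model gives a conditional odds ratio. Under the rule, which of these is reported, and with which covariates, is settled only once the baseline data have been tested.

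**Working it through.** **1. The plan's own figure.** Inputs from Sample size calculation: "we expected that 60% of the participants on the acupuncture arm would achieve adequate relief" and "up to 25% of those on the waitlist arm would achieve such an outcome", two-sided 0.05, 80% power, 20% dropout. With mean proportion (0.60 + 0.25)/2 = 0.425:

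n = [1.960·√(2·0.425·0.575) + 0.842·√(0.60·0.40 + 0.25·0.75)]² / 0.35² = 30.1 per group.

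30.1/0.8 = 37.6, so 38 per group and 76 in total. The stated figure reproduces, and nothing below changes it.

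**2. Selection of one variable.** At level 0.05 under randomisation, P(selected) = 0.05 and P(left out) = 0.95, whatever its prognostic value. Simulated trigger rates were 4.5% to 5.4%.

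**3. At least one trigger among k variables.** For independent tests, P = 1 − 0.95^k. The article gives no k. The outcome section suggests about 11 measures (dyspepsia VAS, NDI-K, EQ-5D index, EQ-5D VAS, costs, FD-QoL, BDI, state and trait anxiety, total and unacylated ghrelin), plus sociodemographic items.

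| k (assumed) | P(at least one), independent |
|---|---|
| 5 | 23% |
| 10 | 40% |
| 11 | 43% |
| 15 | 54% |
| 20 | 64% |

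Independence is generous, since several of these scales probably correlate. By simulation with k = 11, the chance is about 37% at a common correlation of 0.3 and 31% at 0.5.

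**4. What the model switch does to the reported effect.** The planning rates imply a marginal odds ratio of (0.60/0.40)/(0.25/0.75) = 4.5. Suppose a standard normal covariate x has log odds ratio b per SD. For each group, solve for the intercept a at which the average of 1/(1 + exp(−a − bx)) equals 0.25 or 0.60. The difference in intercepts gives a conditional odds ratio of 4.9, 6.1 and 8.2 for b = 0.5, 1.0 and 1.5. The same treatment effect would thus be reported on different scales according to the baseline tests.

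**5. Primary outcome, power.** Simulated at 60% against 25%, with one covariate and 6,000 replicates per setting:

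| n per group | b (assumed) | χ² | Protocol rule | Prespecified logistic | Gain over rule (points) |
|---|---|---|---|---|---|
| 38 | 0.5 | 88.3% | 88.2% | 89.5% | 1.3 |
| 38 | 1.0 | 88.3% | 88.8% | 92.4% | 3.6 |
| 38 | 1.5 | 88.3% | 89.2% | 95.5% | 6.4 |
| 30 | 0.5 | 80.1% | 80.3% | 81.0% | 0.7 |
| 30 | 1.0 | 80.2% | 80.9% | 85.3% | 4.4 |
| 30 | 1.5 | 80.3% | 81.4% | 90.2% | 8.8 |

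**6. Continuous secondary outcomes.** The group-by-time contrast from baseline to week 4 acts as a change score. With equal variances at both times and baseline-outcome correlation r, its variance is proportional to 2(1 − r). ANCOVA gives 1 − r². The ratio is (1 + r)/2, so the reduction is (1 − r)/2. Power is for an assumed effect of 0.65 SD at 38 per group.

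| r (assumed) | Change score | ANCOVA | Reduction | Power, change score | Power, ANCOVA |
|---|---|---|---|---|---|
| 0.3 | 1.40 | 0.91 | 35% | 66% | 83% |
| 0.5 | 1.00 | 0.75 | 25% | 80% | 90% |
| 0.7 | 0.60 | 0.51 | 15% | 95% | 97% |

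**7. Type I error of the rule.** Simulated under the null at 38 per group. Continuous outcome (unadjusted follow-up comparison unless triggered): 0.051, 0.047 and 0.035 at r = 0.3, 0.5 and 0.7. Binary outcome (null rate 25% in both groups): 0.047, 0.049 and 0.041 at b = 0.5, 1.0 and 1.5. The rule is nominal to conservative.

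**The case against.** The best defence is that the rule is written down in advance and applied by a statistician blinded to allocation, so nobody can choose the model to favour one arm. It also does some good when it fires. In the continuous simulation at r = 0.5 and 38 per group, trials with a significant imbalance had an unadjusted rejection rate of 0.17 under the null, and adjustment brought it back to 0.05. An unadjusted χ² test is, moreover, a valid primary test in a randomised trial. All of this stands, and it keeps the point to efficiency and clarity. But prespecified adjustment gives the same protection, also for imbalances that fall short of significance, and does so in every trial.

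Four stronger readings are tempting and are not supported.

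- **Inflated type I error.** A reader might infer this from any two-step procedure. Step 7 shows no inflation.
- **Baseline ignored in the secondary outcomes.** It is not. It enters the repeated-measures analysis as a time level, and is only used less efficiently than as a covariate.
- **Baseline VAS known to be prognostic.** The article does not show this. The primary outcome is a repeated yes/no question on relief, and entry requires a VAS above four points, which may narrow its range. Its value is an assumption.
- **A large loss on the primary outcome.** The 15% to 35% variance figures do not apply to the binary outcome, where the loss is a few points unless the covariate is very strong.

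The article also does not say outright that an adjusted analysis replaces the unadjusted one. Replacement is the natural reading, but if both were reported it would be unclear which is primary.

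**Conclusion.** The point holds as a defect in a stated rule, not as detail left to an analysis plan. Significance testing of chance differences should not select covariates. A given prognostic variable is omitted about 95% of the time, and some adjustment is triggered in roughly a third to a half of trials for 10 to 15 variables, depending on their number and correlation. The rule recovers almost none of the available gain: on the primary outcome at 38 per group its power is within one point of the plain χ² test.

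The size of the loss rests on assumed correlations, effect size and log odds ratios, none of which the article gives. It is modest for the primary outcome and can be substantial for continuous secondary outcomes when r is low. The conclusions remain valid in the type I error sense. This should be changed, but it does not invalidate the trial.

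**What to change.** - Keep the baseline table descriptive and delete the significance trigger.
- Fix one primary analysis in advance, adjusted for hospital (the randomisation stratum) and one named baseline symptom measure, whatever the baseline data show. Dyspepsia VAS is a candidate, its prognostic value being assumed. State the effect measure too; a standardised risk difference from the logistic model would stay close to the comparison of proportions used for planning. The planning rates imply about 0.60·38 + 0.25·38 = 32 responders and 44 non-responders, enough for treatment plus two covariates.
- Analyse each continuous secondary outcome by ANCOVA, or by a repeated-measures model of the follow-up values only, with its own baseline value and hospital as prespecified covariates.

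If the sponsor prefers an unadjusted χ² test as primary, naming it unconditionally would also remove the data dependence, but would forgo the precision.

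The cost is analysis wording. The baseline measures are already scheduled, hospital is known for everyone, the sample size stands, and the article reports recruitment as ongoing with no interim analysis, so the change can be made before outcome data are analysed.

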#### Primary outcome

The primary outcome, PR at 4 weeks, will be compared between groups using the *χ*^2^ test or logistic regression.

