In this trial, partially-individualized manual acupuncture treatments based on the traditional meridian theory and consensus by the experts in acupuncture and FD, will be given. The number of inserted needles per participant per session ranges from 9 to 19. The acupuncture points consist of basic points and optional points. All participants will be given needling at nine fixed points: Large Intestine 4, Stomach (ST) 36, Liver 3, and Spleen 4 bilaterally, and Conception Vessel 12 unilaterally. The optional points include Gallbladder (GB) 21, Small Intestine (SI) 14, Pericardium (PC) 6, Extra acupoint of Head and Neck (EX-HN) 5, and ST 34. These optional points will be selected according to the participant’s symptoms such as headache (EX-HN5), shoulder or back pain (GB21, SI14), nausea and/or vomiting (PC6), and heartburn or epigastric pain (ST34). Two additional Ah-Shi points in the medial scapular region will be allowed in case of shoulder or back pain.

The questions about symptoms related to optional points will be asked to participants by the clinical research coordinator to minimize the bias induced by contact between doctor and participant.

A sterilized stainless steel needle (40 mm length and 0.25 mm diameter; Dongbang Acupuncture Inc., Bundang, Sungnam, Korea) will be used. The depth of needle insertion will be from 5 mm to 30 mm and needle manipulation to achieve ‘de qi’ sensation will be performed. The acupuncture needles will be retained for 15 min.

All acupuncture treatments will be provided by the same Korean Medicine Doctor at each hospital, who will have undergone 10 hours of training and simulation to ensure that they are able to provide identical acupuncture treatment in accordance with a pre-defined protocol.

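### Allocation is blocked within each hospital, but no stated analysis accounts for hospital; the primary test is then conservative if hospitals differ, at a small cost in power that is free to remove

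*Protocol article*

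**What the plan says.** **Allocation.** Under Randomization, "the participants in each hospital will be randomly assigned to one of the two groups using block randomization". Blocks are formed within hospital, so hospital is a stratum of the design. The block size is not given.

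**Primary analysis.** Under Statistical analysis, Primary outcome: "The primary outcome, PR at 4 weeks, will be compared between groups using the" chi-square "test or logistic regression". No covariate or stratum is named, and there is no rule for choosing between the two methods.

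**Adjustment rule.** Under the description of baseline characteristics and homogeneity: "If there are baseline characteristics showing statistical significance between groups, analysis of covariance (ANCOVA) or logistic regression will be used". This is the only stated route by which a covariate enters an analysis.

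**Secondary analyses.** The repeated-measures model has two factors, group and time. Dichotomous outcomes are compared by chi-square test or logistic regression, and adverse events by chi-square or Fisher's exact test. Hospital appears in none of these.

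**Centre size and practitioner.** Under Sample size calculation, each hospital first recruits 30 and the remaining 16 are recruited competitively. Under Intervention, Acupuncture treatment: "All acupuncture treatments will be provided by the same Korean Medicine Doctor at each hospital".

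**The concern.** Stratified allocation forces the arms to be alike in hospital mix. The difference between arms therefore varies less from trial to trial than it would under simple randomisation. An unstratified test does not know this. It counts between-hospital variation as noise, and its standard error is too large whenever the hospitals have different responder rates. The actual significance level then falls below the nominal 5% and some power is given away.

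The adjustment rule cannot be relied on to repair this. It looks for baseline characteristics that differ between arms, whereas hospital is the one characteristic that the design keeps equal between arms. At stake is a little precision in the primary comparison and its confidence interval. The validity of a positive result is not at stake.

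**Working it through.** **1. The plan's own figure.** Inputs from Sample size calculation: 60% on acupuncture, 25% on waitlist, two-sided 5%, 80% power. The mean rate is (0.60 + 0.25)/2 = 0.425.

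n = [1.960 × √(2 × 0.425 × 0.575) + 0.8416 × √(0.60 × 0.40 + 0.25 × 0.75)]² / 0.35²
= [1.960 × 0.6991 + 0.8416 × 0.6538]² / 0.1225 = 30.1 per group.

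This agrees with the article. With 20% dropout, 30.1/0.8 = 37.6, so 38 per group and 76 in total, also as stated.

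**2. Would the adjustment rule bring hospital in?** Assume 38 participants per hospital and 38 per arm, with 19 + k against 19 − k in one hospital and the reverse in the other. The chi-square for hospital by arm is 76 × (76k)²/38⁴ = 0.2105k². To exceed 3.84, k must be at least 5 (0.2105 × 25 = 5.26; k = 4 gives 3.37). That is 24 against 14 in each hospital, in opposite directions. In permuted blocks the running difference within a hospital is at most half the block size, so a difference of 10 needs blocks of at least 20. The block size is not stated, so the accurate wording is hardly ever, not never.

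**3. Size of the conservatism under the null.** The documents give no rates by hospital. I assume two equal hospitals with rates a and b averaging 25%, the planned waitlist rate. The ratio of the true variance to the one the unstratified test uses is

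r = ½[a(1 − a) + b(1 − b)] / [0.25 × 0.75],

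and the actual level is about 2[1 − Φ(1.96/√r)]. For 10% and 40%: r = ½(0.09 + 0.24)/0.1875 = 0.88 and 1.96/√0.88 = 2.089, giving 0.037. The unstratified standard error is too large by a factor of 1/√0.88 = 1.07.

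This was checked by simulation: 300,000 trials per case, 19 per arm per hospital, Pearson chi-square against Cochran-Mantel-Haenszel (CMH) by hospital, no continuity correction.

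| Rates in the two hospitals | r | Level by formula | Chi-square | CMH |
|---|---|---|---|---|
| 25% / 25% | 1.000 | 0.050 | 0.051 | 0.050 |
| 20% / 30% | 0.987 | 0.0485 | 0.049 | 0.049 |
| 15% / 35% | 0.947 | 0.044 | 0.044 | 0.048 |
| 10% / 40% | 0.880 | 0.037 | 0.038 | 0.050 |
| 5% / 45% | 0.787 | 0.027 | 0.028 | 0.049 |

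**4. Power.** Same set-up, with a 35-point effect in both hospitals and 38 per group:

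| Gap between hospitals | Chi-square | CMH | Gain (points) |
|---|---|---|---|
| 0 | 0.883 | 0.883 | 0 |
| 10 points | 0.886 | 0.886 | 0 |
| 20 points | 0.889 | 0.895 | 0.6 |
| 30 points | 0.896 | 0.916 | 2.0 |
| 40 points | 0.908 | 0.943 | 3.6 |

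A case with a larger gap gives a similar gain. With 35% and 85% on acupuncture against 8% and 42% on waitlist, power is 0.909 for the chi-square and 0.948 for CMH.

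**5. Unequal hospitals.** At 46 and 30, the most uneven split the recruitment plan allows, the picture is nearly the same. For 15%/35% the levels are 0.044 and 0.049 and the powers 0.895 and 0.901. For 10%/40% the levels are 0.036 and 0.048 and the powers 0.904 and 0.925.

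**The case against.** The strongest reply is that the plan does not commit to an unstratified chi-square. It also allows logistic regression, and a hospital term in that model could be specified in an analysis plan that is not shown. This stands in part: the article cannot be said to fix an unstratified test. But it is not merely silent. It states an adjustment rule, and by step 2 that rule would in practice leave hospital out. The open choice between two methods is itself in the text.

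A reader might infer that the error rate is wrong in the harmful direction. The calculations show the opposite. The unstratified test stays at or below about 5% in every case, and the 0.051 with identical hospitals is small-sample discreteness, not an effect of centre.

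A reader might also infer that the trial falls short of its planned power. It does not. Against a target of 80%, unstratified power at 38 per group is 0.88 or more throughout, and it does not fall as the hospitals diverge. Stratifying offers a gain on top of that.

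Nor does having one practitioner per hospital strengthen the case much. The waitlist arm receives no acupuncture during the four-week comparison, so a practitioner effect would act on the acupuncture arm alone. That is an interaction of treatment with hospital, which a hospital stratum or main effect does not model. The article also describes 10 hours of training meant to make treatment identical.

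Finally, gaps of 30 to 40 points between two hospitals of one university, with common eligibility criteria, have no support in the documents. That is fair, and it is why the point is minor.

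**Conclusion.** The mismatch is real: hospital is a randomisation stratum, and no analysis stated in the article accounts for it. The consequence is conservative and small. Around a 25% rate, the type I error of the unstratified test is about 0.049 for a 10-point gap between hospitals, 0.044 for 20 points and 0.038 for 30 points. The power forgone is under 1 point at 20 points and up to about 4 points at 40 or more. If the hospitals are alike, nothing is lost either way.

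These sizes rest on assumed rates by hospital, near-exact 1:1 balance within hospital, a common hospital effect in both arms, and no dropout. For scale, the plan's own formula gives power of about 0.80 at 30 per group when hospitals do not differ. Severity is minor: a free improvement to a stated method, not a threat to the trial's conclusion.

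**What to change.** Replace the open choice in the primary analysis with one named method that accounts for hospital. Either of these would do:

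- a Cochran-Mantel-Haenszel test stratified by hospital, reported with the stratified risk difference and its 95% confidence interval; or
- logistic regression of response on group and hospital.

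State that hospital is included because it is a randomisation stratum, whatever the baseline tests show, and include it as a factor in the secondary between-group models.

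The cost is a line or two of wording. Hospital is already recorded when each participant is randomised, no further data are needed, and the sample size of 76 need not change. By the simulations, the stratified test costs essentially nothing in power if the hospitals turn out alike.
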